**Behavioral interventions (Oviva and Changing Health)–related objectives**
To assess average changes in HbA_1c_ levels, systolic blood pressure, cholesterol, smoking, and body weight or BMI in participants using the intervention (compared with controls and within-person changes).To assess patient uptake, engagement, retention, completion, and health care use (defined for DMW above except for completion, which in the case of the behavioral interventions, will be completion of the course).
**MyCognition-related objectives**
To assess average within-person changes in *diabetes distress scores*.To assess changes in cognition scores.To assess changes in referral rates for traditional psychological interventions (compared with controls and within-person changes).
**Health economics objectives**
To assess the net financial costs of the intervention for the health system.To assess the costs to innovation partners of participating in the Test Beds program.To assess the net financial benefits of intervention for the health system.
**Process evaluation objectives (addressed in a brief narrative report)**
To describe the process through which the study was designed.To explain if the interventions were delivered in line with original plans.To explain if the governance arrangements for the intervention were effective and why.To describe whether the partnership of National Health Services (NHS) with innovator firms worked as intended and why.To describe whether the innovator partnerships resulted in improved technology *pull-through*.To describe whether the NHS has received better products or processes as a result of collaboration, testing, or learning.To describe the benefits to innovation partners of being part of the Test Bed program.To describe whether engagement by each party to the partnership been sufficient and why.To describe whether changes were made during implementation to ensure effective delivery of the intervention and why.To describe whether there were barriers and facilitators to effective delivery (and uptake of technology or services) and how were they overcome or ensured.To describe any unintended consequences that needed to be managed and how was this done.To describe to what extent is the intervention likely to be scalable and why.
**Acceptability objectives**
To explore acceptability of DMW and any adjunct interventions.To explore possible mechanisms of change.To explore barriers and facilitators to engagement and sustained use.To explore any perceived benefits or drawbacks of using DMW and adjunct interventions.To explore and barriers and facilitators to implementation (eg, usability, information technology issues, and skills required).

## Methods

A mixed methods approach will be used [25] using a quantitative study with a nested study using qualitative data collection and analysis.

### Ethics

Ethical approval has been granted for this work through the appropriate governing body: NHS West Midlands Black Country Research Ethics Committee reference 265621 (qualitative research) and North West—Greater Manchester South Research Ethics Committee reference 261268 (full study).

### Quantitative Study

#### Design

DMW, behavioral interventions (Oviva and Changing Health) and MyCognition will be prospective controlled cohort studies. Intervention-related changes in outcomes such as glucose levels will be assessed after adjusting for prospective changes observed in matched cohorts of patients not receiving any intervention.

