#### Enrollment and Informed Consent

Enrollment to the DMW intervention will be facilitated through the website, and patients will be directed to the participant information sheet. Providing patients are aged ≥18 years and have a diagnosis of T2D, they will be able to express their interest in taking part in the study by submitting their contact details via the DMW website. Patients will register for web-based services via their general practitioner (GP) who will confirm their identity by checking their documentation. Patients are required to use these web-based service codes to register for DMW and answer a number of inclusion and exclusion criteria. Once registered (and where they match the criteria), the study consent form will be introduced. If and when completed and submitted, the patient’s account is activated, and they are enrolled in the study. When registered, but not matching the study criteria, the patient will be given access to DMW, but not entered into the study or consent process.

Enrollment to other digital interventions will also occur via the DMW website. On the basis of the inclusion and exclusion criteria, participants enrolled and using the DMW intervention will be invited to take part in additional substudies involving an additional digital intervention (Oviva or Changing Health allocated to alternate eligible participants or MyCognition). The above procedure for communicating participant information and obtaining informed consent will be repeated.

We will invite participants to enroll with either Oviva or Changing Health behavioral interventions until 600 have attended each intervention. These interventions will be offered to alternate participants enrolling with DMW, ensuring that the numbers receiving each intervention remain similar.

All DMW participants will be provided with the option of completing the MyCognition web-based cognitive assessment and will be offered the MyCognition intervention until 1000 have completed the intervention. When 1000 people have completed the intervention, DMW participants will continue to be offered the option of completing the MyCognition web-based cognitive assessment but will not be offered the MyCognition intervention. Participants will be invited to complete the MyCognition web-based cognitive assessment every 3 months during the study (a maximum of 3 times). Those completing these assessments, but without receiving the intervention, will act as a control group.

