#### Comparison Group

Within the short time frame available for the study, a randomized controlled trial will not be possible; therefore, the effectiveness of the interventions will be compared with groups of people choosing not to take up the offer of interventions. Data on this comparison group will be sourced from NHS Digital as part of the national GP Data for Planning and Research program. The comparison group will be sourced from patients registered in GM, the other inclusion and exclusion criteria being applied. Controls (not using the intervention) will be matched (up to 10:1) with study participants on age (+2 or −2 years), gender, ethnicity, and general practice. When appropriate, we will increase the number of controls per participant to enable additional matching on baseline levels of outcome measures, such as HbA_1c_ levels. Where there are clinically important differences between participants and controls in relation to other characteristics such as prevalent cardiovascular disease, we will include these variables as covariates regression models.

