### Overview of Data Items and Source of Data by Intervention in the Quantitative Study

#### Diabetes My Way

To evaluate the DMW intervention, the University of Manchester will obtain participant data from GP records via DMW, between April 1, 2016, and March 30, 2022. These data will include the following: age, sex, ethnicity, GP postcode (to assess the degree of socioeconomic deprivation) [35], diabetes type and duration, blood pressure, cholesterol, creatinine, estimated glomerular filtration rate (eGFR), smoking and body weight, height, BMI, medication, diabetes clinic attendance in primary care, and hospital visits including emergency visits.

Participant data from DMW or NHS Digital will also include ethnicity (self-provided, sometimes unreliable from primary care due to missing data), user experience or usability, service use (medication, diabetes clinic attendance in primary care, and hospital visits including emergency visits), and website activity.

Data on control participants (not using DMW) will be obtained from NHS Digital, from April 1, 2016, to March 30, 2022, and will include the following: age, sex, ethnicity, GP postcode (to assess socioeconomic deprivation), diabetes type and duration, blood pressure, cholesterol, creatinine, eGFR, smoking and body weight, height, BMI, medication, diabetes clinic attendance in primary care, and hospital visits including emergency visits.

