#### Behavioral Interventions: Oviva and Changing Health

To evaluate the behavioral interventions, Oviva and Changing Health, the University of Manchester will obtain participant and control data from GP records via DMW and NHS Digital for the period April 1, 2016, to March 30, 2022, as described for DMW. Data on user experience or usability from Oviva and Changing Health participants will be transferred to the University of Manchester via DMW.

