#### Sample Size Calculations

##### DMW, Oviva, and Changing Health Evaluations

The primary outcome for participants and controls receiving usual care is the HbA_1c_ level after the intervention. With a ratio of 1:10 for participants to controls and assuming an SD of 15 mmol/mol in HbA_1c_ levels [39], a total of 86 participants and 430 controls provides 80% power to detect an HbA_1c_ level difference in means of 5 mmol/mol (5% significance level), which is considered the smallest clinically significant HbA_1c_ change. Assuming that 90% of participants provide data after the intervention, this requires a total of 96 participants.

Therefore, we aim to recruit at least 288 participants (96×3) to DMW from which recruitment to the 2 behavioral interventions (Oviva, n=96 and Changing Health, n=96) will occur.

If the required sample size for any intervention is not achieved, appropriate consideration will be given to the interpretation of the results in light of the large number of objectives and outcomes.

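### Oviva and Changing Health are used only on top of DMW but compared with people using neither, so the planned contrast estimates DMW plus programme and cannot be credited to the programme alone

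*Protocol article*

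**What the plan says.** **Who enters the programmes.** Under Enrollment and Informed Consent, "participants enrolled and using the DMW intervention will be invited to take part in additional substudies involving an additional digital intervention". Oviva and Changing Health are allocated to alternate eligible DMW enrollees. The sample size section for DMW, Oviva and Changing Health sets a minimum of 288 DMW recruits, "from which recruitment to the 2 behavioral interventions (Oviva, n=96 and Changing Health, n=96) will occur". Every programme user is therefore a DMW user.

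**Who they are compared with.** The Design section makes one statement for DMW, the behavioural interventions and MyCognition together: intervention-related changes "will be assessed after adjusting for prospective changes observed in matched cohorts of patients not receiving any intervention". The sample size section agrees: "The primary outcome for participants and controls receiving usual care is the" HbA1c level after the intervention.

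Other sections are looser:
- Comparison Group says effectiveness will be "compared with groups of people choosing not to take up the offer of interventions", and then describes controls as not using the intervention, in the singular.
- The DMW data section says "Data on control participants (not using DMW) will be obtained from NHS Digital".
- The data section for Oviva and Changing Health takes participant and control data from GP records via DMW and from NHS Digital, "for the period April 1, 2016, to March 30, 2022, as described for DMW".
- The section on NHS Digital data refers to a cohort not receiving the intervention.

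**What is to be concluded.** Textbox 1 gives the behavioural interventions their own objective, and Textbox 3 gives them change in HbA1c as primary outcome. The sample size section allots 96 participants to each programme. The Abstract's Methods say that the cost-effectiveness work will concentrate on how each intervention affects risk factors and costs.

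**The concern.** If all programme users and no controls use DMW, the difference between them contains whatever DMW does. Covariate adjustment cannot remove it. DMW use is not among the covariates listed under Analysis and, in this comparison, it coincides exactly with programme use. The within-person analysis does not help either, because it again follows people who are using both.

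A coaching programme that adds nothing could thus be reported as lowering HbA1c because the platform does. In the opposite case, a real programme effect could not be told apart from the platform's effect. A statement about how each intervention changes HbA1c is therefore not supported for Oviva or Changing Health.

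**Working it through.** **Inputs** (all from the sample size section for DMW, Oviva and Changing Health): SD 15 mmol/mol, difference 5 mmol/mol, 5% significance level, 80% power, 86 participants and 430 controls, 90% providing data. A two-sided test is assumed, since sidedness is not stated.

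**1. The plan's own figure.** With k controls per participant, n = (1.960 + 0.842)² × SD² × (1 + 1/k) / difference².
- k = 5: 7.849 × 225 × 1.2 / 25 = 84.8, so 85. The plan states 86.
- k = 10: 7.849 × 225 × 1.1 / 25 = 77.7, so 78.
- Allowing for loss: 86 / 0.9 = 95.6, so 96, as stated.

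The figures reproduce at 1:5 (430/86 = 5), not at the 1:10 that the text gives. That is a separate inconsistency, and nothing here depends on it. The 86 v 430 actually stated is used below.

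**2. Probability of a significant result when the programme adds nothing.** Let d be the effect of DMW alone. SE = 15 × √(1/86 + 1/430) = 1.772. The two-sided probability is Φ(d/SE − 1.96) + Φ(−d/SE − 1.96). The article gives no value for d, so a range is assumed. Matching is taken to remove all other differences.

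| Assumed d (mmol/mol) | Probability of p < 0.05 |
|---|---|
| 1 | 8.7% |
| 2 | 20.4% |
| 3 | 39.5% |
| 4 | 61.7% |
| 5 | 80.6% |

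At d = 1, about 0.6 of the 8.7 percentage points fall in the wrong direction; from d = 2 upwards that part is negligible. In every row, the estimate read as the programme's effect is shifted by the whole of d. The last row is the design power at the plan's own target difference.

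**3. What a comparison with DMW-only users could show.** Suppose 86 v 86 evaluable people.
- Unadjusted levels: SE = 15 × √(2/86) = 2.287. Power for 5 mmol/mol = Φ(5/2.287 − 1.96) = 58.9%. The difference detectable with 80% power is 2.802 × 2.287 = 6.4 mmol/mol.
- For 80% power at 5 mmol/mol: 7.849 × 225 × 2 / 25 = 141.3, so 142 per group, or 158 after 10% loss.
- Adjusted for baseline with an assumed correlation r, SD becomes 15 × √(1 − r²): 12.0 at r = 0.6 (power 78%) and 10.7 at r = 0.7 (power 86%).

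**The case against.** **It is a package.** The introduction describes the services as forming a package offered through DMW, and the primary aim concerns DMW and the adjunct interventions together. For a package, DMW plus programme against usual care is a legitimate contrast, and no section claims an effect over and above DMW. This stands in part: the planned estimate is valid and useful for the combination. It does not justify a separate conclusion about each programme, which is what the separate objective, primary outcome, sample size and the Abstract's cost-effectiveness statement lead a reader to expect.

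**The comparator is not fixed.** Wording such as not using the intervention, and control data arriving via DMW, could admit DMW users who declined a programme. The cross-reference to the DMW section may cover only dates and data items. This also stands in part: the wording is inconsistent and needs reconciling. But the two most specific statements, in Design and in the sample size section, describe people with no intervention or with usual care, and no section says that DMW-only users will serve as controls for these programmes. For MyCognition, by contrast, Enrollment and Informed Consent does describe a control group from within DMW.

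**The DMW-only group is hypothetical.** From 288 − 2 × 96 = 96, a reader might infer that a ready comparison group sits unused in the study. The article does not support that. It defines no DMW-only arm, offers the programmes to alternate enrollees until 600 have attended each, and reports 316 enrolled by May 10, 2021. DMW-only users would therefore largely be people who declined or were ineligible, in unknown number. This objection stands in full and limits the fix.

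**The effect sizes are assumed.** This also stands. The probabilities illustrate what would follow if DMW had those effects; they are no evidence that it has.

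**Conclusion.** The point holds as one of attribution. As planned, the HbA1c contrast for Oviva and for Changing Health estimates DMW plus programme against neither. It cannot be assigned to the programme alone. The bias in such an assignment equals the effect of DMW itself, which the article does not give. Over an assumed 1 to 5 mmol/mol, an inert programme would reach significance in about 9% to 81% of studies at 86 v 430 and SD 15.

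Two stronger conclusions might be drawn and are not supported. One is that the contrast with non-users is invalid; it is sound in principle for the combination, subject to the self-selection that any non-randomised comparison here carries. The other is that a comparison with DMW-only users should become the definitive measure of the programme's effect. That group is also self-selected and its size is not assured, so the comparison would exchange one bias for another.

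**What to change.** 1. In Textbox 1, Design, Textbox 3 and the sample size section, label the contrast with non-users *DMW plus Oviva* and *DMW plus Changing Health*, and limit conclusions to that combination.
2. Reconcile the control definitions in Comparison Group, in the data section for Oviva and Changing Health and in the NHS Digital section with those in Design and the sample size section. State in one place whether users of DMW alone can be controls for the programmes.
3. Add a supporting contrast of each programme's users with DMW participants using neither programme, adjusted for baseline HbA1c, age, sex, ethnicity and time since DMW activation. The NHS Digital section already has DMW report which programme each participant uses; confirm that this is carried into the file returned for analysis.
4. Report that contrast as observational. Say who the DMW-only users are likely to be, that their number is not guaranteed, and that power is lower: about 59% for 5 mmol/mol at 86 v 86 on levels, and higher with baseline adjustment, depending on the correlation.

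The cost is some rewording and one further analysis of data already planned. The price is a narrower claim for each programme and a less favourable power figure for the programme-specific question. The relabelling is needed even if the added contrast proves too small to be informative.

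### Oviva and Changing Health are open only to DMW users but are compared with usual care, so the contrast estimates DMW plus the adjunct and cannot be credited to the adjunct

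*Protocol article*

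**What the plan says.** - **Comparator.** The Design section covers DMW, the two behavioral interventions and MyCognition together. Changes are assessed after "adjusting for prospective changes observed in matched cohorts of patients not receiving any intervention". The Comparison Group section says effectiveness is "compared with groups of people choosing not to take up the offer of interventions". For DMW, controls are people not using DMW; the data section for Oviva and Changing Health refers back to the DMW description. The sample size section describes controls as receiving usual care.
- **Entry to the adjuncts.** Under Enrollment and Informed Consent, "participants enrolled and using the DMW intervention will be invited to take part in additional substudies involving an additional digital intervention". The route is the platform itself: "Enrollment to other digital interventions will also occur via the DMW website".
- **Allocation of the offer.** In the same section: "These interventions will be offered to alternate participants enrolling with DMW, ensuring that the numbers receiving each intervention remain similar". Alternation applies to eligible participants and runs until a cap of 600 per intervention.
- **Size.** "we aim to recruit at least 288 participants (96×3) to DMW", with 96 for Oviva and 96 for Changing Health drawn from them.
- **Objectives.** Textbox 1 gives the behavioral interventions their own HbA1c objective, separate from DMW's. Textbox 3 makes HbA1c change the primary outcome for all three.

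**The concern.** Every adjunct user has DMW and no control does. Within that contrast DMW and adjunct are completely confounded, and no covariate adjustment can separate them. A positive result for Oviva or Changing Health could come from DMW, from the motivation that led someone to enrol and then accept a second program, or from the adjunct.

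The confounding also runs the other way. Alternate eligible enrolees are offered one adjunct or the other, so an estimate for all DMW enrolees includes whatever the adjuncts add.

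The article's discussion looks ahead to service-wide change if DMW and the linked behavioral programs work. A health service deciding whether to pay for an adjunct on top of DMW needs the increment, which the stated contrast does not supply.

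**Working it through.** **1. What each contrast estimates.** Write *d* for the effect of DMW alone, *a* for the adjunct's added effect and *s* for residual self-selection after matching, and assume the effects add.
- Adjunct users versus usual care: *d + a + s*. With *a* = 0 the expected value is *d + s*.
- All DMW enrolees versus usual care: *d* + (share using Oviva × its effect) + (share using Changing Health × its effect) + *s*.
- Within-person change: the HbA1c baseline closes on July 1, 2019, and DMW was offered from August 2019. The adjunct users' change therefore also contains *d*.

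**2. Reproducing the planned size.** Inputs from the sample size section: SD 15, difference 5 mmol/mol, 5% significance (two-sided reproduces the figure), 86 participants, 430 controls.
- SE = 15 × √(1/86 + 1/430) = 1.772.
- 5 / 1.772 = 2.822; power = Φ(2.822 − 1.96) = 80.6% (80.4% by noncentral t).
- 86 / 0.9 = 95.6, so 96.

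The figures match a 1:5 ratio, which is 86:430, not the 1:10 in the text. That is a separate matter.

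**3. Chance that an inert adjunct reaches significance.** Set *a* = 0 and *s* = 0, use the same SE, and let *d* vary. The article gives no DMW effect, so *d* is assumed. P = Φ(*d*/1.772 − 1.96) + Φ(−*d*/1.772 − 1.96).

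| Assumed *d* (mmol/mol) | *d*/SE | P(significant) |
|---|---|---|
| 0 | 0 | 5% |
| 1 | 0.564 | 9% |
| 2 | 1.129 | 20% |
| 3 | 1.693 | 39% |
| 4 | 2.257 | 62% |
| 5 | 2.822 | 80% |

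**4. Who is DMW-only.** Three groups: those who decline the adjunct, those ineligible for it, and those enrolling after the caps. With 316 enrolled by May 10, 2021, the caps of 600 each were far off. No stated HbA1c analysis uses DMW-only users as a comparator. MyCognition differs: people who complete its assessments without the intervention serve as its controls.

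**5. What the existing alternation could support.** Compare Oviva-offered with Changing Health-offered enrolees, 86 versus 86 with data.
- SE = 15 × √(2/86) = 2.287.
- The reductions cited in the introduction differ by 12.8 − 4 = 8.8. At full uptake, 8.8 / 2.287 = 3.847 and power is about 97%.
- At 50% uptake of both offers, with no effect of an offer not taken up, the gap is 4.4. Then 4.4 / 2.287 = 1.924 and power is about 49% (48% by noncentral t).
- For a realized difference of 5, 5 / 2.287 = 2.186 and power is about 58% (noncentral t; 59% by the normal approximation).

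**The case against.** **The comparator wording is not uniform.** The Comparison Group section also describes controls simply as not using the intervention. Adjunct control data come through both DMW and NHS Digital, and adjunct use is flagged for each participant, so DMW-only users could be identified and used. This stands as an ambiguity, but the Design, data-source and sample size sections all point to patients without DMW.

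**The plan may want only a package effect.** The article presents the offer as a combined package, and the behavioral objective asks for change in users compared with controls, not an increment over DMW. This stands in part: as a package estimate the contrast answers a real question. A reader might infer that the adjunct objectives cannot be answered at all; the documents do not support that. What fails is crediting the result to the adjunct.

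**The 80% figure is one end of a range.** The 5 mmol/mol is the smallest clinically significant change, not an expected DMW effect. This stands. Calling 80% the false-positive rate would go too far. If DMW has no effect, this component of the bias vanishes and only self-selection remains.

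**DMW-only users do exist.** A reader might infer that everyone who enrols gets an adjunct offer, so that only decliners are left. The eligibility condition and the caps rule that out.

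**The 97% figure is a best case.** It needs full uptake, and the 8.8 gap subtracts associations from separate evaluations of 204 and 41 people. The uptake figures in the article for other programs are low, about 15% for structured education in Greater Manchester and about 13% for DMW in Scotland. This stands and limits what the by-offer analysis can show.

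**Conclusion.** The concern holds as a matter of attribution. As stated, the Oviva and Changing Health HbA1c contrasts estimate DMW plus adjunct versus usual care, with self-selection, and support no claim about either adjunct alone. The expected error for an inert adjunct is DMW's whole effect. The chance of a significant result runs from 5% to 80% as that unknown effect runs from 0 to 5 mmol/mol, assuming additive effects, SD 15, 86 versus 430 and no residual selection. The DMW estimate has the mirror-image problem wherever adjunct users are included, and no exclusion of them is stated.

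A reader might also infer that, since offers already alternate, new enrolees should be randomized with a delayed-offer arm. That does not follow. The plan states "Within the short time frame available for the study, a randomized controlled trial will not be possible". Such an arm would change the design, consent and ethics approval and would postpone an offer. At 86 versus 86 it would have at most about 58% power for 5 mmol/mol, where 142 per group with data are needed for 80%.

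**What to change.** 1. **Relabel and restrict.** Name the NHS Digital contrasts *DMW plus Oviva versus usual care* and *DMW plus Changing Health versus usual care* in the objectives, outcomes and analysis text, and state that no adjunct-specific claim will be drawn from them. State also that the DMW estimate includes any adjunct use. Cost: wording only.
2. **Use the allocation that already exists.** The plan says "These interventions will be offered to alternate participants enrolling with DMW". Add an HbA1c analysis of eligible enrolees by the offer allocated, Oviva versus Changing Health, regardless of uptake. DMW use is common to both groups, and acceptance of the offer does not determine group membership. Cost: one extra model and a record of which offer each enrolee was allocated.

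The second analysis should be described as supportive. It compares the adjuncts with each other, so two equally effective programs would show no difference, and it cannot show that either adds to DMW alone. Its power depends on uptake, so uptake of each offer should be reported beside it.
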